### **Objective 2bis (WP 1 to 6)**

The difference between the post-intervention measures (18 months) and the measures made 29 months after the end of the intervention for all cognitive, psychoaffective, life factors, sleep measures (and blood and imaging measures depending on budget availability) will be assessed within the 2 interventional groups. Analyses of the effect of the exposure to meditation/English learning (number of hours of practice, number of sessions...) will also be performed.

### **Objective 2ter (WP 1 to 6)**

The difference between post-intervention (18 months) and long-term (29 mois +/- 6 mois months after the end of the intervention) measures in all cognitive, psychoaffectives, life factors, sleep assessments (and blood and imaging measures depending on budget availability) will be compared between the 2 interventional groups. The exposure to meditation/English learning (number of hours of practice, number of sessions...) will also be compared between the 2 interventional groups and taken into account when relevant.

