## **2.2. Secondary objectives**

### **2.2.1. Secondary objectives in relation to the interventions**

**OBJECTIVE 2:** To compare the effects of the two interventions (meditation and foreign language learning, for 18 months) with each other and with a passive control in non-meditating seniors, on behavioural and biological measurements (cognitive, psycho-affective, blood, sleep, and imaging), including measurements to assess potential deleterious effects as well as gender-specific effects (men/women);

**OBJECTIVE 2 bis:** To estimate the maintenance of the effect of the interventions (meditation and foreign language learning) in the long term (29 months after the end of the intervention) on cognition, psycho-emotional factors, sleep, and lifestyle (and imaging and blood markers if the budget allows).

**OBJECTIVE 2 ter:** To compare the long-term effects (29 months after the end of the intervention) of the 2 interventions (meditation and foreign language learning) with each other on cognition, psycho-emotional factors, sleep, and lifestyle (and imaging and blood markers if the budget allows).

**OBJECTIVE 3:** To estimate the effect of the interventions (meditation and foreign language learning, for 18 months) on the volunteers' entourage (i.e., their perception of the volunteers' changes, their interaction with the volunteer, and their willingness to help the volunteer), compared to a passive control.

**OBJECTIVE 3 bis:** To compare the long-term effects of the interventions (meditation and foreign language learning) on the volunteers' entourage (i.e., their perception of the volunteers'

changes, their interaction with the volunteer, and their willingness to help the volunteer) 29 months after the intervention ended.

**OBJECTIVE 3 ter:** To estimate the effect of the interventions (meditation and foreign language learning, for 18 months) (i.e. their acceptance of the intervention, their perception of the changes...).

**OBJECTIVE 3 quater:** To assess the consistency between participants' perceptions of the interventions and their effects and those of the meditation or English teachers (after the interventions have ended).

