| Days and half days of intensive meditation practice                                       | X                |                        |                       |               |
| Weekly group language courses                                                             |                  | X                      |                       |               |
| Daily language training at home                                                           |                  | X                      |                       |               |
| Days and half days of intensive language practice                                         |                  | X                      |                       |               |
| Completion of diary/questionnaire for intervention follow-up                              | X                | X                      |                       |               |
| V2: Intermediate evaluation visit at 9 months                                             | X                | X                      | X                     |               |
| Neuropsychological and behavioural assessment V2 (1 session)                              | X                | X                      | X                     |               |
| V3: End of intervention visit                                                             | *                | *                      | *                     |               |
| Medical interview                                                                         | X                | X                      | X                     |               |
| Series of examinations identical to V1                                                    | X                | X                      | X                     |               |
| Qualitative interview about the intervention experience                                   | X                | X                      | -                     |               |
| V4: Visit 29 months post-intervention                                                     | X                | X                      | X                     |               |
| Medical interview                                                                         |                  |                        |                       |               |
| Identical series of examinations at V1 and V3 (except PET-Amyvid and polysomnography)     | X                | X                      | X                     |               |

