### **6.11. Visit no.4 – Follow-up visit 29±6 months post-intervention**

29±6 months (35 months) after the end of the procedure, each participant will be seen for a long-term follow-up visit. This visit will include the same examinations as those performed in V1 and V3 except polysomnography and PET-Amyvid® examination.

The Cumulative Illness Rating Scale (CIRS) score will also be calculated, combining medical, biological, neuropsychological, and polysomnographic data collected at visits 1, 3, and 4.

Polysomnography is the reference method in this field, but it is extremely time-consuming and requires expertise both for the installation of electrodes and sensors and for the analysis of the tracings. During

the long-term follow-up of the participants, we will use a simpler and faster tool than polysomnography. The Dreem headband is a new EEG measurement tool that appears to be as accurate as polysomnography. It comes in the form of a headband with 5 dry electrodes (i.e. not requiring the application of a conductive paste) allowing the measurement of brain electrical activity, cardiac activity, respiratory rate and movements. It is easily placed on the participant's head, without any prior preparation. It takes less than three minutes to fit the headband to the participant's head and to move the hair away from the contact points of the electrodes. This headband will make it easier to collect sleep data, and will be proposed several consecutive nights at the participant's home in order to evaluate the impact of sleep variability, which is practically impossible with polysomnography.

In MRI2 session, the QSM sequence will not be performed because the signal-to-noise ratio does not allow to obtain usable scans. (Many QSM sequences in V1 and V3 are not valid.) It will be replaced by a 10-minute high-resolution DTI Locus sequence (HR-DTI-Locus), complementary to the HPC-T2 scan to understand the precise links between hippocampal substructures (HPC-T2), their connectivity and locus coeruleus substructures (HR-DTI-Locus) (Betts et al., 2019 Brain; Treit et al., 2018 Neuroimage).

[figure not shown]

Figure 8: Course of the MRI2 examination in V4 (the time spent in the MRI is indicated in orange with a total duration at the Cyceron center of approximately 120 min).

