The participation of the persons to the present protocol will be registered on the national file of the persons lending themselves to a biomedical research, managed by the Ministry of Health. Indeed, the non-expert seniors participating in this research will receive an indemnity for the constraints suffered and in compensation for the travels carried out within the framework of this research up to 600€ at the inclusion, 200€ at intermediate, 800€ at the end of the intervention, and finally 500€ (if they accept the optional long-term follow-up) at the end of their participation in this research. The senior experts will receive a compensation of 550€ upon inclusion and will be reimbursed upon presentation of receipts for expenses related to their participation in this trial. This indemnity will be due to them in proportion to their participation in the research. It will be paid in full only if they participate in all the visits, examinations and tests planned by the research.

They are not allowed to participate simultaneously in any other research during a 12-month exclusion period.

For participants in the "passive control" group who wish to do so, it will be proposed to finance a 2-month MBSR (Mindfulness Based Stress Reduction) meditation course (2h/week for 8 weeks + 1 day) or an English course (module: 15h-20h), at the end of the trial. This internship must be completed within 6 months after the end of the interventions.

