#### Secondary objectives

○ In relation to the interventions studied:

OBJECTIVE 2: To compare the effect of an 18-month mindfulness-based intervention, an 18-month intervention based on language learning and no intervention, on areas of cognition, psycho-affective/emotion, compassion, support, mindfulness, sleep, wellbeing, quality of life, and on biological and radiological measures, including sex-specific effects;

OBJECTIVE 2bis: To estimate the maintenance of the effects of the interventions (mindfulness-based training and language learning) 29 mois +/- 6 mois months after the end of the intervention on areas of cognition, psycho-affective/emotion, compassion, support, mindfulness, sleep, wellbeing, quality of life (and on biological and radiological measures depending on budget availability);

OBJECTIVE 2ter: To compare the long-term effects (29 mois +/- 6 mois months after the end of the intervention) of the two interventions (the 18-month mindfulness-based intervention and the 18-month intervention based on language learning) on areas of cognition, psycho-affective/emotion, compassion, support, mindfulness, sleep, wellbeing, quality of life (and on biological and radiological measures depending on budget availability);

OBJECTIVE 3: To compare the effect of an 18-month mindfulness-based intervention and of an 18-month intervention based on language learning vs. no intervention on participants' partners (perception of participant's changes, interactions with the participant, willingness to help the participant).

OBJECTIVE 3bis: To estimate the effects of the interventions (meditation and foreign language learning) on participants' partners (perception of participant's changes, interactions with the participant, willingness to help the participant) 21 months after the end of the intervention.

OBJECTIVE 3TER: To estimate the effects of the interventions (meditation and foreign language learning, during 18 months) (acceptance of the interventions, perception of changes...).

○ Without relation to the interventions studied:

OBJECTIVE 4: To estimate the association between meditation practice and behavioral and biological measures (cognition, psycho-affective, lifestyle, blood, sleep and radiological measures), by comparing expert meditators and participants with no previous meditation practice;

OBJECTIVE 5: To identify neural signatures of mindfulness and compassion meditations in senior expert meditators;

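### Objective 2ter asks for the long-term effect, but its analysis measures decay after 18 months; Objective 2bis measures decay without a control arm

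*Combined protocol and SAP*

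**What the plan says.** Protocol section 2.2.1 states Objective 2ter as "To compare the long-term effects (29 months after the end of the intervention) of the 2 interventions". The secondary SAP repeats the aim ("To compare the long-term effects (29 mois +/- 6 mois months after the end of the intervention) of the two interventions") and words Objective 2bis as "To estimate the maintenance of the effects of the interventions".

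The secondary SAP then sets these analyses:

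- **Objective 2ter:** "The difference between post-intervention (18 months) and long-term (29 mois +/- 6 mois months after the end of the intervention) measures", compared between the meditation and English arms.
- **Objective 2bis:** the same 18-month-to-V4 difference, which "will be assessed within the 2 interventional groups".

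Neither analysis uses the baseline value or the passive control arm. Yet the flow chart in protocol section 6.2 gives all three randomised arms a V4 visit: "Identical series of examinations at V1 and V3 (except PET-Amyvid and polysomnography".

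**The concern.** A long-term effect of a randomised intervention is a difference between arms at the late visit, with baseline as the common starting point. Starting the clock at 18 months puts any benefit already gained into the reference value. The 2ter contrast then shows which arm lost more, not which arm is better off.

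A lasting advantage would be reported as no long-term difference, and a vanished one as an advantage for the other arm.

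In 2bis, about 29 months of ageing, partly during the pandemic, would be read as failure to maintain the effect. Protocol section 1.2.1 itself expects brain volume and perfusion to fall with age.

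**Working it through.** **1. The plan's own figure.** The only power statement for the randomised arms concerns the primary endpoints: effect size 0.75, 80% power, two-sided 1.25% (5%/4), 42 per arm. A noncentral t calculation gives 80.9% power at 42 per arm, so the figure reproduces. The documents give no effect size, SD, between-visit correlation or dropout rate for V4.

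**2. Algebra for 2ter.** Let d3 and d4 be the meditation-minus-English differences at 18 months and at V4, with the arms equal at baseline by randomisation. Let r = d4/d3 be the share kept.

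- Planned contrast: (V4 − V3) in meditation minus (V4 − V3) in English = d4 − d3 = −(1 − r)·d3.
- Baseline-to-V4 contrast: d4 = r·d3.

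With d3 = 0.5 SD (assumed):

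| Share kept | True difference at V4 | Planned 2ter contrast |
|---|---|---|
| 1 | +0.50 | 0 |
| 0.5 | +0.25 | −0.25 |
| 0 | 0 | −0.50 |

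A time trend common to both arms cancels. The zero and the signs do not depend on any assumed SD.

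**3. How often 2ter would point the wrong way.** Two-sided 5% (secondary SAP, type I error section), no further dropout. The noncentrality is (d/change SD)·√(n/2).

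- Benefit fully lost (contrast −0.50), change SD 1: at 50 per arm 0.5 × √25 = 2.5, giving 70% in favour of English; at 45 per arm 65%; at 35 per arm 54%. Fifty is the planned size. Forty-five is one third of the 135 seniors named in the lockdown annex. Thirty-five allows for further loss, since protocol section 14.5 calls the long-term follow-up optional.
- Same case, visit SD 1, correlation 0.6 to 0.8: change SD = √(2(1 − ρ)) = 0.89 to 0.63, giving 79% to 98% at 50 per arm.
- Half kept, visit SD 1, same correlations, 50 per arm: 28% to 50% in favour of English, although meditation is still 0.25 SD better at V4.
- Fully maintained: 2.5% in favour of meditation, the same as for two interventions that never differed. The baseline-to-V4 contrast would find the difference 70% of the time (change SD 1, 50 per arm).

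**4. Objective 2bis.** Paired t test, n = 50, change SD 1, effect fully maintained, ageing decline g from 18 months to V4 (assumed). The noncentrality is g·√50.

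| g (SD) | Noncentrality | Chance of a significant change |
|---|---|---|
| 0.1 | 0.71 | 11% |
| 0.2 | 1.41 | 28% |
| 0.3 | 2.12 | 55% |

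**5. Is the missing comparison supplied elsewhere?**

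- The mixed models under Objective 2 stop at 18 months.
- The general delta convention refers to D00, but the specific 2bis and 2ter text replaces that with 18 months.
- Objective 9 uses baseline, 18 months and V4 together, but only in passive controls and partners.
- Objective 3bis compares three groups, but on partner questionnaires and again from 18 months.
- Protocol section 11.3 describes no V4 analysis.

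**The case against.** **Change since the end of the intervention is the natural measure of maintenance.** This stands for 2bis: zero is the intended reading, and with no between-arm test there is no sign reversal. What remains is the absence of a control for ageing and period. In addition, no equivalence margin is set, so a non-significant change would not show maintenance. Objective 9 will describe the control trajectory but does not set it against the intervention arms.

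**A reader of both Objective 2 and 2ter could add d3 and d4 − d3 to recover d4.** True of the point estimates. But the test and interval that the plan attaches to 2ter belong to the decay contrast, and the sum is not a planned analysis.

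**Reversal needs a real difference at 18 months that then shrinks.** This stands. If the arms gain and lose equally, the contrast stays at zero.

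**Two stronger readings are tempting but not supported.**

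- One might infer that sleep differences will mix devices, since at V4 "we will use a simpler and faster tool than polysomnography". Polysomnography is not performed at V4, nothing says that headband values will be subtracted from it, and Table 6 schedules sleep questionnaires at both V3 and V4. One clarifying sentence is enough.
- One might infer that the MBSR or English course offered to passive controls ("This internship must be completed within 6 months after the end of the interventions") distorts 2bis or 2ter. As written, neither analysis uses passive controls. The course matters only once they become the V4 reference.

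**Conclusion.** The 2ter analysis does not estimate the quantity named in its objective. This follows from the algebra and needs no assumed numbers. For 2bis the narrower point holds: ageing and the pandemic period are uncontrolled, although passive controls attend the same visit.

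The probabilities are illustrations only. A 0.5 SD difference fully lost favours the comparator about 54% to 70% of the time with change SD 1 and 35 to 50 per arm, or 79% to 98% at 50 per arm with visit SD 1 and correlation 0.6 to 0.8. A fully maintained effect in 2bis is accompanied by a significant change about 11% to 55% of the time for ageing declines of 0.1 to 0.3 SD. No single figure is established.

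A reader might infer that the trial's main conclusions are at risk. They are not: the primary endpoints and the main secondary outcome compare change from inclusion to 18 months. Severity: should fix.

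**What to change.** - **2ter:** define the estimand as the meditation-minus-English difference at V4 adjusted for baseline, from one mixed model with V1, V3 and V4 and all three arms. State that missing=failure imputation is not used in this model.
- **2bis:** report each intervention's baseline-adjusted difference from passive control at V4 beside the same difference at V3.
- **18-month-to-V4 change:** keep it as a separate analysis labelled as decay. Objective 3bis uses the same 18-month reference and needs the same review.
- **Passive controls' course:** record whether, when and which course was taken, and examine uptake in a model-based sensitivity analysis. Do not simply set course-takers' V4 values to missing: the secondary SAP's missing=failure rule would then give them the failure value and bias the contrast towards the interventions.
- **Sleep:** state that polysomnography variables, not collected at V4, are not differenced against headband values.

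Cost: SAP wording and one added variable for course uptake. All visits and arms are already scheduled.

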### **Objective 3bis**

The difference between measures from partners' questionnaires obtained post-intervention (18 months) versus 29 mois +/- 6 mois months later (i.e. 29 mois +/- 6 mois months after the end of the intervention) will be compared between the three groups. (see Section “*Descriptive analysis*” above for comparative methods).

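### Objectives 2ter and 3bis concern long-term effects, but the secondary SAP compares change from 18 months to V4, which measures what happens after the intervention and not the long-term effect

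*Combined protocol and SAP*

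**What the plan says.** **The questions.** Protocol section 2.2.1 states Objective 2ter as "To compare the long-term effects (29 months after the end of the intervention) of the 2 interventions (meditation and foreign language learning) with each other". The secondary SAP, under Secondary objectives, asks the same: "To compare the long-term effects (29 mois +/- 6 mois months after the end of the intervention) of the two interventions". For partners, Objective 3bis in the protocol begins "To compare the long-term effects of the interventions (meditation and foreign language learning". The secondary SAP words 3bis as estimating the effects on partners, and dates it 21 months after the intervention where its own analysis section says 29 ± 6.

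Maintenance is a separate objective, 2bis, which opens "To estimate the maintenance of the effects of the interventions (mindfulness-based training and language learning". Its analysis is the 18-month-to-V4 difference within each intervention arm.

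**The planned analyses.** For 2ter the analysis variable is "The difference between post-intervention (18 months) and long-term (29 mois +/- 6 mois months after the end of the intervention) measures in all cognitive", psychoaffective, lifestyle and sleep domains (blood and imaging if the budget allows), compared between the two intervention arms. For 3bis it is "The difference between measures from partners' questionnaires obtained post-intervention (18 months) versus 29 mois +/- 6 mois months later", compared between the three groups.

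**Elsewhere in the secondary SAP.** The general convention for change subtracts the D00 value. Objectives 2 and 3 compare change from inclusion to 18 months, and the Objective 2 mixed models end at 18 months. Objective 9 names inclusion, 18 months and V4 together, but for passive controls and partners, not as a comparison of arms.

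**The concern.** V3 is taken at the end of the intervention, so any effect is already in it. Subtracting V3 from V4 removes that effect and leaves only what changed afterwards. Compared between arms, the result answers whether one arm lost more than the other since the end of training. It does not answer whether the arms differ at V4 because of the intervention, which is what 2ter asks.

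As written, 2ter is the between-arm version of 2bis, and the long-term question has no planned analysis. At stake is the interpretation of the V4 visit: a null result could sit alongside a durable advantage, and a significant result could favour the arm that is worse off at V4.

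**Working it through.** **1. The plan's own figure.** Protocol section 11.2 gives 42 per group for an effect size of 0.75, 80% power and two-sided 1.25%. A noncentral-t calculation gives 80.9% power at 42 and 79.7% at 41, so the figure is reproduced. It covers the primary comparisons only. The documents state no size, effect or power for 2ter or 3bis.

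**2. The identity.** Let D3 be the between-arm difference in mean change from inclusion to 18 months, and D4 the same from inclusion to V4 (the long-term effect). The planned contrast is

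P = (V4 − V3) in meditation − (V4 − V3) in comparator = D4 − D3.

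This is algebra and holds for any set of participants seen at all three visits. Ageing drift common to the arms cancels. Writing D4 = f × D3, where f is the retained share of the *between-arm* difference, P = (f − 1) × D3:

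- f = 1: P = 0.
- f between 0 and 1: P has the opposite sign to D4.
- f above 1 (the gap widens after 18 months): P has the right sign but falls short of D4 by D3.

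**3. The same in terms of arms.** With 18-month gains gM and gE (in SD) and retained fractions rM and rE:

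P = gM(rM − 1) − gE(rE − 1); D4 = gM·rM − gE·rE.

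| gM | gE | rM | rE | D4 | P |
|---|---|---|---|---|---|
| 0.75 | 0 | 100% | – | +0.75 | 0.00 |
| 0.75 | 0 | 75% | – | +0.56 | −0.19 |
| 0.75 | 0 | 50% | – | +0.375 | −0.375 |
| 0.75 | 0.25 | 50% | 50% | +0.25 | −0.25 |
| 0.75 | 0.25 | 100% | 50% | +0.625 | +0.125 |
| 0.75 | 0.50 | 80% | 50% | +0.35 | +0.10 |
| 0.75 | 0.25 | 100% | 0% | +0.75 | +0.25 |

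The gains and fractions are illustrative. The first three rows have a comparator that neither gains nor fades, the case closest to the passive controls in 3bis. The last three have a comparator that loses more after 18 months: the sign is right, the size is not.

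**4. Illustrative probabilities.** From the documents: 50 per arm (protocol section 3.2) and two-sided 5% for other secondary endpoints (secondary SAP, Type I error rate). Assumed: D3 = 0.5 SD and a correlation of 0.7 between any two visits. The SD of a change is √(2 × (1 − 0.7)) = 0.775.

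- *f = 1.* Planned standardised contrast 0, so 5% rejection. V4 minus inclusion: 0.5/0.775 = 0.65, power 89%.
- *f = 0.5.* Planned: −0.25/0.775 = −0.32, a 36% chance of significance for the wrong arm and 0.02% for the right one. V4 minus inclusion: +0.32, power 36% for the right arm.
- *Correlation 0.5 to 0.8, f = 0.5:* wrong-arm chance 24% to 50%.
- *45 per arm* (the Lockdown annex records 135 seniors on 8 April 2020; 135/3 = 45 if even), correlation 0.7: 89% becomes 86% and 36% becomes 33%.
- *D3 = 0.75 SD, f = 0.5, correlation 0.7:* wrong-arm chance 67% at 50 per arm, 62% at 45.

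**The case against.** **The long-term effect is recoverable.** Objective 2 gives the between-arm change from inclusion to 18 months and 2ter gives 18 months to V4. Their sum is the V4-minus-inclusion contrast, apart from differences in who is observed, and 2bis and 2ter can be read as a pair on persistence. This stands as far as it goes: the 18-month-to-V4 contrast is a valid measure of differential maintenance. But no summed estimate, interval or test is planned, and maintenance already has its own objective. The general D00 convention does not help either, because the text for 2ter and 3bis names 18 months explicitly.

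**A reader might infer that any retained benefit scores zero and any partly retained one scores as harm.** The documents do not support that as a general statement. The comparator in 2ter is English, an active arm for which protocol section 1 expects a benefit of its own, so it may fade too. The outcome then depends on which arm loses more in absolute terms, as the table shows.

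**A reader might infer that both documents ask, for partners, which intervention is better in the long term.** Only the protocol says compare; the secondary SAP says estimate the effects. Neither wording describes change after 18 months.

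**A reader might infer that the trial will report no long-term difference.** The secondary SAP prescribes no such conclusion, so this is a risk of misreading and not something the plan commits to.

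**The probabilities are favourable.** The effect size, retention and correlation have no source in the documents for these outcomes. Protocol section 14.5 calls the long-term follow-up optional, so 50 per arm at V4 is a ceiling. Equal correlation between visits is also generous to the inclusion-based contrast, since V1 to V4 spans the longer interval. These objections bear on the figures, not on the identity.

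**Conclusion.** The mismatch is real. The planned contrast for 2ter and 3bis equals the V4 effect minus the 18-month effect, and no planned between-arm analysis uses inclusion as the reference for V4. That conclusion rests on the text and on algebra, with no numerical assumption.

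The direction of the error is conditional. If the comparator is stable after 18 months, a fully retained benefit has an expected contrast of zero and a partly retained one has the wrong sign. If the comparator also fades, the sign may be right and the size is still wrong. The probabilities show only that, under plausible values, the problem would not be hidden by noise.

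It should be fixed, but it is not critical to the trial. Both objectives are secondary. The four primary comparisons and the main secondary outcome are all at 18 months and are unaffected.

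**What to change.** In the secondary SAP, Objectives 2ter and 3bis:

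- Make the long-term comparison V4 with inclusion as the reference: V4 minus V1, or V4 adjusted for V1, for example by extending the Objective 2 mixed model to V4. Compare two arms for 2ter and three groups for 3bis.
- Where a measure has no V1 value, compare V4 levels between groups. Sleep recorded by the headband that replaces polysomnography at V4 (protocol section 6.11) is one case.
- Keep the 18-month-to-V4 change as a separate analysis labelled maintenance.
- Align the wording of 3bis between protocol and SAP, including the 21-month figure left in the SAP objective.

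Report the V4 contrast with its confidence interval. At half retention its power is only about one in three under the assumptions above, so a non-significant result would not show equivalence.

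The cost is about two sentences. No new data are needed: V1 is already collected for most measures, and Objective 3 already uses partners' inclusion questionnaires. The change also brings both analyses into line with the SAP's own definition of change.
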